#### Participant timeline {13}

The procedure of the study is presented in a flow diagram (Fig. 1). The SPIRIT Figure for this study is provided in Fig. 2.

**Fig. 1 Fig1:**
[figure not shown]
Flow diagram NUMOQUA

**Fig. 2 Fig2:**
[figure not shown]
SPIRIT figure NUMOQUA

### Sample size {14}

An a priori power calculation was performed using G-Power [78] and establishing an ANOVA (F-test) between two measures and two groups for the primary endpoint, the quality of life subscale of the Knee Injury and Osteoarthritis Outcome Score, demonstrating that 50 participants (25 in each group) are required to reveal differences at the 5% significance level, with 90% power, using large effect size (1.1) as reported by previous studies [79, 80]. A change of 8–10 points is considered the minimally important change (MIC) and the standard deviation is set to 15 [81]. Considering a 20% drop-out ratio, we decided to include 30 participants per group (60 participants in total).

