### Interventions

#### Explanation for the choice of comparators {6b}

The research question was based on the PICO (Patient, Intervention, Comparison, Outcome) principle and reads as follows: The effects of the GLA:D® training programme combined with the nutrition therapy Austrian OA Cuisine - compared to the GLA:D® training programme alone - on quality of life in patients with knee osteoarthritis. To answer this research question, a randomised controlled clinical trial is conducted.

Both the intervention group and the control group participate in the GLA:D® training programme, which has already been shown to reduce pain and improve function as well as QL [15]. To examine the synergistic effects, the intervention group receives, in addition to the GLA:D® programme, training and counselling concerning the implementation of the developed nutrition therapy named Austrian OA Cuisine (see {11a}). The control group receives general information about a healthy lifestyle.

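### The stated effect size of 1.1, the 8–10 point MIC, the SD of 15 and the 50 participants do not fit together, and the 90% power does not carry over to an MIC-sized difference

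*Protocol article*

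**What the plan says.** All the figures stand in one paragraph of the protocol article, Sample size {14}. The calculation is described as a G-Power F-test (ANOVA) with two measures and two groups on the KOOS quality-of-life subscale. Its result is a total of 50, split evenly between the arms and tested at 5%. The power and the effect behind that total are given as "with 90% power, using large effect size (1.1) as reported by previous studies". The next sentence, citing a different source, says: "A change of 8–10 points is considered the minimally important change (MIC) and the standard deviation is set to 15". A 20% drop-out allowance then takes enrolment to 30 per group.

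The paragraph does not say whether 1.1 is Cohen's d or Cohen's f, whether it is a within-group or a between-group effect, whether 15 is the SD of a score or of a change, or what correlation between the two measures was entered. Statistical methods {20a} puts the focus on T0 against T4 (12 months).

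**The concern.** A sample-size paragraph should let a reader go from the inputs to the number. Here the inputs point to different trials. An effect of 1.1 and an SD of 15 imply a target well above the only difference in points that the paragraph names, and the obvious readings of 1.1 do not return 50.

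What is at stake is the meaning of the 90%. The MIC is the only yardstick in points that the article gives for the primary outcome. If power at that yardstick is far below 90%, a non-significant T4 comparison would leave an MIC-sized benefit of the diet open, and the stated power would give no hint of this.

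**Working it through.** **Inputs, all from Sample size {14}:** significance level 5% (taken as two-sided, as an F-test between two groups is); power 90%; effect size 1.1; MIC 8–10 points; SD 15; 25 per group; two groups, two measures. The correlation ρ between measures is not given, so it is varied.

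**1. Do the inputs agree?**
- 1.1 × 15 = 16.5 points.
- 8/15 = 0.53 and 10/15 = 0.67.
- 16.5/10 = 1.65 and 16.5/8 = 2.06, so 1.1 SD is 1.65 to 2.1 times the MIC.

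**2. Does 1.1 reproduce 50?**

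(a) As Cohen's d, two-sample comparison. Power comes from the non-central t distribution with 2n − 2 degrees of freedom and non-centrality d·√(n/2). With d = 1.1, 18 per group give 89.4% and 19 per group give 91.0%, so 19 per group (38 in total) are needed. At 25 per group the power is 96.8%, not 90%.

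(b) As Cohen's f, repeated-measures ANOVA with m = 2. Non-centrality is f²·N·m/(1 + (m − 1)ρ) for the between-groups effect and f²·N·m/(1 − ρ) for the group-by-time interaction, with 1 and N − 2 degrees of freedom. With f = 1.1 and ρ from 0 to 0.9, N is 4–12 in total.

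(c) As d = 1.1 converted to f = 0.55 in the same ANOVA. With ρ from 0 to 0.9, N is 6–36 in total.

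(d) As a between-arm difference in change of 1.1 score SDs. The SD of a change is 15·√(2(1 − ρ)), so the standardised effect is 1.1/√(2(1 − ρ)). N is 72, 52, 50, 38 and 24 at ρ = 0, 0.3, 0.31, 0.5 and 0.7. This reading returns 50, but only with a correlation that is not in the text.

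**3. What do 25 per arm deliver if 15 is the SD of the compared quantity?**
- 8 points (d = 0.533): power 45.5%.
- 9 points (d = 0.600): 54.7%.
- 10 points (d = 0.667): 63.7%.
- 90% power is reached at d = 0.936, and 0.936 × 15 = 14.0 points.
- 90% power at the MIC would need 49 per arm (10 points) to 75 per arm (8 points).
- Half-width of the 95% CI: 2.011 × 15 × √(2/25) = 8.5 points.

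**4. What if 15 is a score SD and change scores are compared?** With 25 per arm:

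| ρ | SD of change | Power at 8 points | Power at 10 points |
|---|---|---|---|
| 0.3 | 17.7 | 34.5% | 49.7% |
| 0.5 | 15.0 | 45.5% | 63.7% |
| 0.7 | 11.6 | 66.5% | 84.6% |

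Change-score power reaches 90% at ρ of about 0.75 for 10 points and 0.84 for 8 points. With baseline adjustment, where the SD is 15·√(1 − ρ²), the corresponding correlations are about 0.70 and 0.82.

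**The case against.** The best defence is that the paragraph makes two separate statements. The 90% is tied to 1.1, taken from earlier studies. The MIC and SD come from another source and may be there only to help interpretation. An MIC is also a change, and the text does not name it as the between-arm target. All of this stands. A reader might infer that the article promises 90% power for the MIC and breaks that promise, but it makes no such promise. The defect is a set of inputs that are not reconciled.

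A reader might also infer that 1.1 cannot lead to 50. Reading (d) shows that it can, with ρ near 0.31. What holds is that 50 does not follow from the inputs as stated. Reading (d) also does not help at the MIC: at ρ = 0.3 the power at 8–10 points is only 34.5–49.7%.

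Under the plain d reading, 50 is more than 1.1 requires. That is true, and it means that any shortfall concerns only smaller differences.

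A further tempting step is to call 16.5 points unrealistic, since both arms receive GLA:D®, "which has already been shown to reduce pain and improve function as well as QL" (Explanation for the choice of comparators {6b}), so that the randomised contrast is only what the diet adds. The article gives no size for that added effect and the cited studies are not at hand, so the step cannot be supported. It is still fair to ask whether 1.1 is a within-group or a between-group figure.

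Finally, the analysable number need not be 25 per arm. Thirty less 20% is 24 (44.0% at 8 points, 61.8% at 10). Thirty per arm with complete data would give 52.8% and 71.9%. Neither changes the picture.

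**Conclusion.** The point holds in this form: the effect size, the MIC and the SD are not reconciled, the 50 cannot be reproduced from the stated inputs, and the stated 90% should not be read as applying to 8–10 points. If 15 is the SD of the compared quantity, or a score SD with a correlation of 0.5, power at the MIC with 25 per arm is 45.5–63.7%. If 15 is a score SD and change scores are compared, it is 34.5–84.6% over correlations of 0.3 to 0.7. Only correlations of about 0.75 (10 points) to 0.84 (8 points), or 0.70 to 0.82 with baseline adjustment, would bring it to 90%, and the article gives no such value. The figures assume a two-sided 5% test and equal arms.

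**What to change.** Restate Sample size {14} without changing enrolment, since recruitment has ended:
- Say whether 1.1 is d or f, and whether it is a within-group or a between-group effect.
- Say whether SD 15 describes a score or a change, and which correlation was entered.
- Correct the N or the power that then follows from 1.1.
- State the between-arm difference detectable with 90% power (about 14 points if 15 is the SD of the compared quantity), and the power at 8–10 points over a range of correlations, as in the table above.
- Commit to reporting the T4 between-arm difference with its 95% CI against the MIC (expected half-width about 8.5 points under the same SD).

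The cost is rewording, and a stated power that looks less favourable.

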### Trial design {8}

This study is a parallel-group, two-arm superiority RCT to evaluate the impact of the nutrition therapy Austrian OA Cuisine combined with an evidence-based training programme (GLA:D®) in patients with mild to moderate knee OA in Lower Austria. The treatment combination of the nutrition therapy Austrian OA Cuisine and the GLA:D® training programme is compared with the treatment involving the GLA:D® training programme only.

Participants are informed about all aspects of the study and asked to sign a consent form. Participants are randomised at a 1:1 ratio (see {16a}). Staggered recruitment will be carried out to expand the recruitment phase and to handle all participants’ appointments and trainings more easily.

The duration of the intervention is 9 months. Within this intervention period, the intervention group undergoes the GLA:D® training programme for the first 6 weeks and receives the Austrian OA Cuisine for 9 months. The control group undergoes the GLA:D® training programme for 6 weeks and receives general information regarding a healthy lifestyle. During the 3 months follow-up phase, the intervention group members are expected to implement the Austrian OA Cuisine as well as the exercises of the GLA:D® training programme on their own into their daily life.

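### The 20% drop-out allowance was added to 50 instead of divided out: 60 enrolled leave 48 after 20% loss, slightly below the required 50

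*Protocol article*

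**What the plan says.** Everything needed stands in one paragraph of the protocol article, Sample size {14}. The requirement is given first: "50 participants (25 in each group) are required", "at the 5% significance level, with 90% power", with the power calculation described as "establishing an ANOVA (F-test) between two measures and two groups for the primary endpoint" and "using large effect size (1.1) as reported by previous studies". The enrolment target follows: "Considering a 20% drop-out ratio, we decided to include 30 participants per group (60 participants in total". Drop-out is the only reason given for going from 50 to 60, and the section does not define the drop-out ratio further. Trial design {8} sets equal allocation: "Participants are randomised at a 1:1 ratio".

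**The concern.** A drop-out percentage is ordinarily a share of those enrolled. On that reading, the target is the required number divided by the proportion retained. The step from 25 to 30 per group is instead a 20% mark-up on the required number, which gives too small a target.

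The three printed figures (50 required, 20% drop-out, 60 enrolled) therefore do not fit together. A reader of the protocol, or of a results paper that repeats the sentence, would believe that the trial can lose one participant in five and still hold its planned sample. It cannot quite do so.

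**Working it through.** **Inputs, all from the protocol article**
- Required number: 50 in total, 25 per group (Sample size {14}).
- Drop-out: 20% (Sample size {14}).
- Enrolment target: 60 in total, 30 per group (Sample size {14}).
- Allocation: 1:1 (Trial design {8}).

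**Reproducing the plan's figure**
- Mark-up, n × (1 + d): 50 × 1.20 = 60 and 25 × 1.20 = 30. This matches exactly.
- Division, n / (1 − d): 50/0.80 = 62.5, rounded up to 63. Per group, 25/0.80 = 31.25, rounded up to 32, or 64 in total with equal groups. This does not match.

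**What 60 delivers**
- Remaining after 20% loss: 60 × 0.80 = 48, and 30 × 0.80 = 24 per group.
- Shortfall against the requirement: 50 − 48 = 2 participants, 1 per group.
- Shortfall at enrolment: 63 − 60 = 3, or 64 − 60 = 4 with equal groups.
- Largest loss that still leaves 50: (60 − 50)/60 = 16.7%.
- Check on 64: 64 × 0.80 = 51.2, which is at least 50.

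**Cost in power**

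The article does not say whether the effect size of 1.1 is Cohen's d or f, and it does not give the correlation between the two measurements. The loss of power is therefore shown under three assumptions, each at a two-sided 5% level:

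| Assumption | 25 per group | 24 per group |
|---|---|---|
| Two-sample t-test, d = 0.936, solved backwards so that 25 per group gives 90% | 90.0% | 88.8% |
| Repeated-measures F-test, f = 1/3, zero correlation (gives N = 50 at 90%) | 90.4% | 89.2% |
| Two-sample t-test, 1.1 read as d | 96.8% | 96.2% |

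The differences are 1.2, 1.2 and 0.6 percentage points. Neither d = 0.936 nor f = 1/3 with zero correlation is stated in the article; they serve only to size the loss if 50 does correspond to 90% power.

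**The case against.** The strongest reply is that the consequence is negligible. That stands: two participants and about one point of power change no decision, and with 1.1 read as Cohen's d, 24 per group would still exceed 90%. This settles how much weight the point carries. It does not make the sentence right.

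Other replies have less force:
- **The ratio might mean drop-outs per completer (10/50).** The article does not say so. If that was intended, the wording still needs changing, because readers will take 20% as the tolerated share of those enrolled.
- **Sixty might come from three intervention rounds of 20.** Concealment mechanism {16b} gives 20 per round, and 3 × 20 = 60. But Sample size {14} names drop-out as the reason, and logistics would not make 60 × 0.8 equal 50.
- **Intention-to-treat analysis with multiple imputation is planned ({20c}), and a mixed linear model for repeated measures ({20a}).** Participants lost before the 12-month visit may still contribute earlier data, so 48 is the number of completers and need not be the number analysed. That is fair, but the sponsor chose to plan enrolment around drop-out, and these methods do not alter that arithmetic.

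Two stronger readings are tempting, and the article does not support either as a consequence of this error:
- **That the allowance leaves the trial badly underpowered.** The article says: "A change of 8–10 points is considered the minimally important change (MIC) and the standard deviation is set to 15". With 8–10 points and SD 15 (d = 0.53–0.67), a two-sample t-test with 24 per group has 44–62% power. With 25 per group it has 46–64%, and with 32 per group still only 56–75%. The low power comes from the gap between that difference and the assumed effect of 1.1, which is a separate question. The drop-out step accounts for only 1–2 points of it.
- **That exclusions under the attendance quota in {11b} come on top of the 20%.** Sample size {14} does not say what the 20% covers, so those exclusions may already be included.

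**Conclusion.** The point holds as a minor arithmetic error. The allowance was added where it should have been divided out, so 60 enrolled tolerate 16.7% loss, not 20%. At 20% loss the trial is 2 evaluable participants (1 per group) below its own requirement, which costs about one percentage point of power if 50 gives 90%.

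The shortfall rests on one assumption: that the 20% is a share of those enrolled, which is the usual meaning and is not contradicted in the article. The size of the power loss also rests on the assumed effect sizes above. The true power at 24 per group cannot be recovered from the article, since the effect-size metric and the correlation between measures are not stated.

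**What to change.** Replace the enrolment sentence in Sample size {14} with: *60 randomised participants (30 per group) retain the required 50 if drop-out does not exceed 16.7%; at 20% drop-out 48 (24 per group) remain, slightly below the requirement.*

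If a power for 24 per group is added, take it from the original G*Power inputs rather than from a value solved backwards.

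The cost is one sentence and a slightly less favourable stated tolerance. Trial status gives January 2024 as the end of recruitment, and no additional participants or design change are needed. The same wording should be carried into the results paper.

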### Recruitment {15}

The St. Pölten University for Applied Sciences has carried out other studies regarding OA in the past, which means that there is a database of people interested in OA studies. In the first step, these are contacted by email and informed about this planned study. Press releases are placed in newspapers and magazines—especially in local ones—and information is posted on social media. Flyers are distributed at relevant congresses, at clinicians specialising in OA, and events at the St. Pölten University of Applied Sciences. Furthermore, networks like self-help groups (OA forum Austria), the Austrian Association of Dietitians and the intranet of the St. Pölten University of Applied Sciences are used to reach out to interested people.

## Assignment of interventions: allocation

### Sequence generation {16a}

After a successful recruitment of suitable participants, they are stratified according to sex, randomised using the *Random Allocation Software* [82] and allocated either to the intervention or to the control group.

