### Concealment mechanism {16b}

Once a consenting number of suitable participants per intervention round (*n* = 20) have been recruited, subjects will be randomised into intervention group (IG) and control group (CG). This is done by allocating participants to a sequential ID number. Using the *Random Allocation Software* [82], these ID numbers are allocated either to the intervention group or to the control group. The Random Allocation Software will not release the randomisation code until the patient has been recruited into the trial.

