## Statistical methods

### Statistical methods for primary and secondary outcomes {20a}

In this study, the focus is on the comparison of data collected at the beginning of the study (T0) and at the end of the study (T4; T0 + 12 months). For all statistical tests, the significance level is set at *p* < 0.05 in accordance with scientific standards. Data are analysed using IBM SPSS Statistics 28 or greater. Normal distribution of metric variables is tested with Shapiro–Wilk-Test and Q-Q-diagrams. For interpreting the results correctly, we also conduct a descriptive analysis showing the arithmetic mean and standard deviation of metric outcome parameters for each group. To control for outliers, we also report the minimum and maximum for each group in addition to a supportive graphical analysis. For interval and nominal scaled variables, we conduct a frequency analysis. To compare the effects of an evidence-based training programme (GLA:D®) with and without the nutrition therapy Austrian OA Cuisine, we conduct an analysis of variance (ANOVA) based on a mixed-linear model of repeated measures looking for assessing effects within each group (e.g. between baseline and the other data collection points) and between groups. In case variables are non-normal or non-metric in scale, we use the Friedman Test, respectively [83]. The group variable (intervention group or control group) serves as the independent variable and the observed outcome parameters (see {12}) serve as the dependent variable.

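### Randomisation is stratified by sex and run per round of 20, but the stated model names only the treatment group; adding both factors is a nearly free improvement

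*Protocol article*

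**What the plan says.** On allocation, the protocol article gives three facts.

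- Sequence generation {16a}: "After a successful recruitment of suitable participants, they are stratified according to sex", and then randomised by software.
- Concealment mechanism {16b}: allocation is done batch by batch. It starts "Once a consenting number of suitable participants per intervention round" is reached, with 20 per round. With 60 participants in all (Sample size {14}), that makes 60/20 = 3 rounds.
- Trial design {8}: "Participants are randomised at a 1:1 ratio". Block size is not given, nor whether the arms are forced to be equal within sex or within round.

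On analysis, Statistical methods for primary and secondary outcomes {20a} states: "we conduct an analysis of variance (ANOVA) based on a mixed-linear model of repeated measures". It adds: "The group variable (intervention group or control group) serves as the independent variable". It also says that "the focus is on the comparison of data collected at the beginning of the study (T0) and at the end of the study" (12 months). Neither sex nor round is named as a factor or covariate there. The section on additional analyses {20b} mentions only optional subgroup analyses and correlations.

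**The concern.** When randomisation is balanced on a factor that predicts the outcome, that factor can no longer contribute to chance differences between the arms. A model without the factor still leaves its variance in the residual. The reported standard error can then be larger than the true one, the confidence interval wider than needed, and the test conservative. In a trial of 60, avoidable loss of power matters. Sex may matter for some secondary outcomes, such as body composition or carotenoids. Round may matter because recruitment ran from October 2022 to January 2024, so rounds differ in calendar time. The documents give no figure for either effect.

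**Working it through.** The plan has no figure of its own on this point, so there is none to reproduce. Whether 50 participants follow from the stated effect size is a separate matter and does not affect what follows.

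**Inputs from the protocol article**
- Sex as stratification factor ({16a}); rounds of 20 ({16b}); 1:1 ratio ({8}).
- SD 15, 25 evaluable per arm, 60 enrolled, minimally important change 8 to 10 points ({14}). A difference of 10 is used for power.

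**Assumptions, not in the documents**
- Sex and round together explain 0%, 10%, 20% or 30% of the variance of the T4 score (sex + round: 0+0, 5+5, 10+10, 20+10).
- 65% of participants are of one sex; the test is two-sided at 5%.

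**Step 1. Standard error reported by the group-only model.** 15 × √(1/25 + 1/25) = 15 × 0.283 = 4.24 points, whatever share R² the two factors explain.

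**Step 2. Ideal case of exact balance.** True SE = 4.24 × √(1 − R²); type I error = 2[1 − Φ(1.96/√(1 − R²))].
- R² = 0.10: SE 4.02, type I error 3.9%
- R² = 0.20: SE 3.79, type I error 2.8%
- R² = 0.30: SE 3.55, type I error 1.9%

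**Step 3. Realistic case by simulation.** 5000 runs per scenario: three rounds of 20, arms balanced within sex and round as far as odd numbers allow, 10 of 60 lost at random, T4 score as outcome, ordinary least squares with group only against group + sex + round. Dropout disturbs the balance, so the effect is smaller than in step 2.

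| Share explained | SE reported, group only | True SE, group only | Ratio | Type I error, group only | Type I error, adjusted | Power at 10 points, group only | Power at 10 points, adjusted |
|---|---|---|---|---|---|---|---|
| 0% | 4.23 | 4.21 | 1.01 | 4.7% | 4.9% | 63% | 62% |
| 10% | 4.23 | 4.08 | 1.04 | 4.1% | 4.9% | 63% | 66% |
| 20% | 4.23 | 3.87 | 1.09 | 3.2% | 4.8% | 65% | 73% |
| 30% | 4.23 | 3.77 | 1.12 | 2.9% | 5.3% | 66% | 78% |

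The power lost is 66 − 63 = 3, 73 − 65 = 8 and 78 − 66 = 12 points at shares of 10%, 20% and 30%.

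**Step 4. Allocation not balanced within sex or round.** With unrestricted allocation the group-only test stayed near nominal (4.8% to 5.7%), so there is no mismatch of standard errors. Only efficiency is lost: power at 10 points is 63% against 65% adjusted (10% share), 63% against 70% (20%) and 62% against 75% (30%). At 0% share, adjusting costs 64% against 61%.

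**Step 5. Change from T0 to T4.** If sex and round shift the score equally at both times, their terms subtract out of T4 − T0. Simulated with balanced allocation, 20% share and an assumed within-person correlation of 0.5: SE 3.78 without and 3.80 with adjustment, type I error 4.8% for both, power 73% and 72%. Nothing is lost, and adjusting gains nothing. Only effects of sex or round on the size of the change would matter.

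**The case against.** The strongest reply has four parts.

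- **The planned contrast is change.** The focus is T0 against T4 in a repeated-measures model. A constant sex difference, for instance in body fat or carotenoids, is already present at T0 and drops out of a group-by-time contrast. This stands and limits the point most. It does not remove it: {20a} also speaks of effects between groups, and sex or round may influence the change itself.
- **Balance within sex and round is not documented.** This also stands. A reader might infer from the mismatch that the trial's standard errors are wrong and its type I error is below 5%. The documents do not support that as fact. It needs restricted allocation, which is plausible but unstated, and prognostic factors, whose strength is not given.
- **The sentence on the group variable is no complete list of model terms.** It does not say that group is the only one, and it omits time, which is plainly in the model. The article is condensed, and an analysis plan that is not shown may list covariates. This is fair, and it makes the point a recommendation to state the terms, not a contradiction. The article does, however, name the model and its independent variable and leaves its own stratification factor out.
- **The consequence is mild.** The estimate is unbiased and the error runs in the conservative direction. Conceded.

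A reader might also infer that a round effect would deal with differences between training groups. It would not. Under Intervention description {11a} and Explanation for the choice of comparators {6b}, the dietetic group sessions go to the intervention arm only. That clustering is nested within arm, and a round effect common to both arms cannot absorb it.

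**Conclusion.** The point holds in a limited form: the model as written does not reflect the two factors used in randomisation. For a group-only comparison of the T4 score, the standard error can be overstated by about 4% to 12%. This rests on balanced allocation within sex and round, SD 15, 50 evaluable participants and assumed variance shares of 10% to 30%. If the two factors explain nothing, or act equally at T0 and T4 and the contrast is change, the loss is nil. There is no risk of bias and, under balanced allocation, none of excess false positives. This is a free improvement, not an error that threatens the conclusions.

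**What to change.** State in the analysis section, or in the analysis plan, that the primary and secondary mixed models include sex (1 df) and intervention round (2 df) as fixed effects. Where the contrast is change over time, add their interactions with time; main effects alone leave a change contrast untouched.

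The cost is one sentence and a few degrees of freedom (1 + 2 = 3 for each comparison of a time point with baseline). If the factors explain nothing, the price is about 1 point of power under balanced allocation (63% to 62%), or about 3 points if allocation were unrestricted (64% to 61%). It would also help to state whether the arms are balanced within sex and within round, since that decides whether the standard error or only efficiency is affected.
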